# Rifapentine- and moxifloxacin-containing short-course regimens for mild spinal tuberculosis: study protocol for a multicenter, randomized, non-inferiority phase II clinical trial

**DOI:** 10.3389/fphar.2025.1684771

**Published:** 2025-12-19

**Keywords:** mild spinal tuberculosis, short-course regimen, rifapentine, moxifloxacin, non-inferiority

## Abstract

**Background:**

Spinal tuberculosis is the most common form of osteoarticular infection, with recommended anti-tuberculosis treatment durations typically being long (9–18 months), even for mild cases, increasing the risks of drug resistance, toxicity, and poor patient adherence. This study aims to explore, in patients with mild spinal tuberculosis, whether a new combination of anti-tuberculosis drugs (containing rifapentine and moxifloxacin) could shorten the treatment duration.

**Methods and Analysis:**

This trial is an open-label, randomized, controlled, non-inferiority trial comparing the efficacy and safety of a short-course regimen [6-month anti-TB regimen] containing rifapentine and moxifloxacin with empirical long-course regimen [12-month anti-TB regimen] in the treatment of patients with mild spinal tuberculosis. Patients diagnosed with mild spinal tuberculosis who meet the inclusion and exclusion criteria will be recruited and randomized in a 1:1 ratio to either of the two arms. Empirical long-course regimen includes rifampin, isoniazid, pyrazinamide and ethambutol (2RHZE/10RH), while short-course regimen includes rifapentine, moxifloxacin, isoniazid and pyrazinamide (2HRtZM/4HRtM). The primary outcomes are TB-recurrence rate at 24 months after completion of treatment and proportion of participants with grade 3 or higher adverse events during treatment with study medications.

**Discussion:**

This trial will provide evidence whether a short-course regimen of anti-TB drugs (2HRtZM/4HRtM) is non-inferior to the empirical long-course regimen (2RHZE/10RH) in patients with mild spinal tuberculosis. If non-inferiority is established, it will contribute to a more optimized treatment for spinal tuberculosis.

**Clinical Trial Registration:**

This study is registered with https://clinicaltrials.gov/ct2/show/NCT06917495 as NCT06917495.

## Introduction

1

Spinal tuberculosis is the most common type of osteoarticular tuberculosis, accounting for approximately 1%–3% of all tuberculosis cases and representing one of the most prevalent types of extrapulmonary tuberculosis (Meier, 1994; Li et al., 2023; WHO, 2024). As a country ranking third among the 30 countries with the highest tuberculosis burden globally, China faces considerable challenges from spinal tuberculosis, with a large number of new cases reported annually—its tuberculosis incidence reaching 52 per 100,000 population in 2023 (Li et al., 2023; WHO, 2023; WHO, 2024). Clinically, spinal tuberculosis poses severe health risks: it accounts for 62% of deaths associated with osteoarticular tuberculosis (Li et al., 2023), and post-tuberculosis sequelae such as spinal deformities, neurological disabilities, and paraplegia are common, significantly impairing patient’s quality of life and imposing long-term physical and psychological burdens (Igbokwe et al., 2023). For children and adolescents, these sequelae can lead to lifelong functional limitations, further exacerbating the public health impact (Igbokwe et al., 2023). Mild spinal tuberculosis, characterized by early-stage or localized spinal involvement (Oguz et al., 2008), constitutes a substantial proportion of spinal tuberculosis cases; these patients are primarily managed with drug therapy, which presents a unique opportunity to explore more optimized treatment strategies and to prevent further disease progression (Oguz et al., 2008).

Anti-tuberculosis (anti-TB) drug therapy is a crucial approach for treating spinal tuberculosis infections, especially in cases of mild spinal tuberculosis (Rajasekaran and Khandelwal, 2013). In guidelines, an extended treatment duration of 9–18 months for osteoarticular tuberculosis is recommended, which is 1.5–3 times longer than the standard 6-month regimen (2HRZE/4HR) typically used for extrapulmonary tuberculosis (Hongqi et al., 2022; WHO, 2022). Beyond the direct health hazards of the diease itself, this prolonged treatment brings additional societal and economic burdens: it increases the risk of drug toxicity (such as hepatotoxicity) (Yew et al., 2018; Maiwall et al., 2024), drug resistance (Zumla et al., 2014) — a growing concern globally as multidrug-resistant TB continues to thwart control efforts (Romano et al., 2020) — and poor patient adherence (Guix-Comellas et al., 2015). These issues not only reduce treatment effectiveness but also lead to increased medical costs and resource comsumption; for patient in low- and middle-income regions or with limited medical access, the long treatment cycle may result in treatment interruption, further worsening the diease burden (Tochukwu et al., 2023).

A pilot study initially explored the efficacy of 6-month and 12-month anti-TB treatments for spinal tuberculosis, showing similar clinical outcomes in both groups (Nene et al., 2019). In addition, a large multicenter randomized controlled trial demonstrated that a new 4-month anti-TB regimen containing isoniazid, rifapentine, moxifloxacin, and pyrazinamide was non-inferior to the standard 6-month regimen (2HRZE/4HR) in treating drug-sensitive pulmonary tuberculosis in terms of efficacy, safety, and tolerability—confirming the synergistic bactericidal potential of these four drugs (Dorman et al., 2021). These findings, combined with the unique pharmacological advantages of rifarentine and moxifloxacin in targeting spinal tuberculosis, provide critical insights into optimizing treatment for mild spinal tuberculosis.

Notably, the 2HRtZM/4HRtM regimen is not the only option but may be the most appropriate, balancing efficacy, safety, and clinical applicability. Alternatives containing bedaquiline or delamanid were excluded because they are primarily recommended for drug-resistant tuberculosis (WHO, 2022) with no evidence in drug-sensitive mild spinal tuberculosis, and their higher costs and stricter safety monitoring (e.g., cardiac QT interval monitoring for bedaquiline) limit accessibility in diverse medical settings—relevant given this study’s 14 centers across China with varying resources. In contrast, rifapentine and moxifloxacin are included in China’s National Drug Catalogue for Basic Medical Insurance (National Healthcare Security Administration, 2024), ensuring cost-effectiveness and broad accessibility.

Therefore, this study aims to investigate whether the rifapentine- and moxifloxacin-containing 6-month anti-TB regimen is non-inferior to a 12-month empirical regimen for the treatment of mild spinal tuberculosis in terms of efficacy and safety through a multicenter, randomized, phase II clinical trial—with the ultimate goal of reducing sequelae, alleviating disease burden, and improving accessibility of effective treatment, particularly in regions with varying levels of medical resources.

## Methods and analysis

2

### Study design

2.1

This is an open-label, multicenter, non-inferiority randomized controlled trial designed to compare the efficacy and safety of a short-course regimen [6-month anti-TB regimen] containing rifapentine and moxifloxacin with an empirical long-course regimen [12-month anti-TB regimen] in the treatment of patients with mild spinal tuberculosis (Table 1). A total of 300 participants will be recruited from 14 study sites in China. The flowchart of this trial is shown in Figure 1.

**TABLE 1 T1:** Diagnostic criteria of mild spinal tuberculosis.

Diagnostic criteria
➢ Mild to moderate neurologic deficits: American spinal injury association grade D or E
➢ Single vertebral involvement with central lesions or multiple vertebral involvement (<3) with marginal lesions
➢ Vertebral appendage tuberculosis without canal involvement
➢ Vertebral body collapse less than 1/3 of the total height
➢ The extent of paravertebral abscess is limited (Confined to single vertebral level, no retropharyngeal abscess or lumbar muscle abscess)
➢ No significant spinal kyphosis (Cobb angle <30°)
➢ No apparent spinal instability (Lateral X-ray shows thoracic sagittal displacement >2.5 mm, and lumbar sagittal displacement >4.5 mm or 15% of vertebral anterior-posterior diameter on static lateral X-ray are considered potentially unstable)

**FIGURE 1 F1:**
[figure not shown]
The flowchart of this trial.

### Population

2.2

The recruitment of eligible patients will be overseen by the clinicians from the attending research teams. Participants or their legal guardians, will be fully informed about the study, and written informed consent will be obtained from all participants or their guardians. Patients are eligible for recruitment if they meet all the inclusion criteria and do not meet any of the exclusion criteria (Table 2).

**TABLE 2 T2:** The eligibility criteria.

Inclusion criteria	Exclusion criteria
Pre-randomization	
1. Age ≥12 years 2. Based on medical history, clinical manifestations, radiological exams, laboratory tests, and possible histological samples, the patient is diagnosed with mild spinal tuberculosis according to the criteria (Table 1) 3. Laboratory test values are obtained within 14 days prior to screening [①serum or plasma ALT ≤3 × ULN; ②serum or plasma TBIL ≤2.5 × ULN; ③serum or plasma creatinine level ≤2 × ULN; ④serum or plasma potassium level greater than or equal to 3.5 mmol/L (Max 5.5 mmol/L); ⑤hemoglobin level of 7.0 g/dL or higher (Max 17.2 g/dL for male, 15.1 g/dL for female); ⑥platelet count of 100,000/mm^3^ or higher (Max 300,000/mm^3^)] 4. Women of childbearing potential who are not surgically sterilized must agree to practice a barrier method of contraception or abstain from heterosexual intercourse during study drug treatment 5. Women of childbearing potential must have a negative pregnancy test at or within 7 days prior to screening 6. KPS ≥60 7. A verifiable address or residence location that is readily accessible for visiting, and willingness to inform the study team of any change of address during the treatment and follow-up period 8. Written informed consent	1. Pregnant or breastfeeding 2. Unable to take oral medications 3. Previously enrolled in similar studies 4. Spinal tumors or metastatic tumors 5. Patients with mental disorders or cognitive dysfunction 6. Have received any investigational drug in the past 3 months 7. Have received more than 5 days of treatment directed against active tuberculosis within 6 months preceding initiation of study drugs 8. Have received more than 5 days of systemic treatment with any one or more of the following drugs within 30 days preceding initiation of study drugs: Isoniazid, rifampin, rifambutin, rifapentine, ethambutol, pyrazinamide, kanamycin, amikacin, streptomycin, capreomycin, moxifloxacin, levofloxacin, gatifloxacin, ofloxacin, ciprofloxacin, other fluoroquinolones, ethionamide, prothionamide, cycloserine, terizidone, para-aminosalicylic acid, linezolid, clofazimine, delamanid or bedaquiline 9. Known history of prolonged QT syndrome 10. Weight less than 40.0 kg 11. Known allergy or intolerance to any of the study medications 12. Individuals will be excluded from enrollment if, at the time of enrollment, their Mtb isolate is already known to be resistant to any one or more of the following: rifampin, isoniazid, pyrazinamide, ethambutol, or fluoroquinolones 13. Other medical conditions that, in the investigator’s judgment, make study participation not be in the individual’s best interest
Post-randomization	
	14. No Mtb is identified in the screening, baseline, and week 2 samples 15. Mtb isolated from or tested by molecular assays (Xpert MTB/RIF) in samples obtained before or after the study are determined to be resistant to isoniazid, rifampin, or fluoroquinolones

ALT: alanine aminotransferase; KPS: karnofsky performance status; Mtb: *Mycobacterium tuberculosis*; TBIL: total bilirubin; ULN: upper limit of normal.

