### Sample size

2.7

We estimated the sample size based on the non-inferiority hypothesis that the TB-recurrence rate of spinal tuberculosis at 24 months after completion of treatment of the short-course regimen will be no worse than the empirical long-course regimen. It is assumed that the TB-recurrence rate in the empirical long-course group is 5% and the rate will be the same in the short-course regimen arm. Considering a 10% dropout rate, a sample size of 150 per arm (300 in total) will give 80% power (one-sided type I error of 5%) to demonstrate a 6.6% non-inferiority margin (Dorman et al., 2021) using Pearson chi-square test with normal approximation. Detailed sample size calculation steps, including the statistical formula, parameter justification, and sensitivity analysis results, are provided in the Supplementary Material.

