### Statistical analysis

2.9

The statistical analyses will be carried out in SAS v9.4 by independent statisticians. Descriptive statistical analysis will be performed by calculating the mean ± SD, median (minimum-maximum, or lower quartile-upper quartile) for continuous variables and counts (percentages) for categorical variables. The statisticians will perform chi-square test or Fisher’s exact test for categorical variables and Student’s test or Wilcoxon rank sum test for continuous variables. It will be considered statistically significant if p value <0.05. The efficacy analysis will use intention-to-treat, per-protocol, and as-treated populations. The concentration of anti-TB drugs will be determined using a validated LC-MS method at the Center for Pharmaceutical Analysis and Testing, School of Pharmaceutical Sciences, Shandong University. NONMEM 7.4 will be used to determine whether the PD targets have been achieved for each participant. Detailed statistical analyses are provided in the Supplementary Material.

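### The post-randomisation exclusion for drug resistance has no time limit, so following it as written can remove recurrences with acquired resistance; the no-Mtb exclusion also relies on an on-treatment week-2 sample

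*Protocol article*

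**What the plan says.** Table 2 (section 2.2, Population) has a block of exclusions that apply after randomisation.

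- Criterion 14 applies when "No Mtb is identified in the screening, baseline, and week 2 samples".
- Criterion 15 applies when Mtb "in samples obtained before or after the study are determined to be resistant to isoniazid, rifampin, or fluoroquinolones".
- Resistance already known at enrolment is handled separately, before randomisation, by criterion 12.
- Inclusion criterion 2 does not require bacteriological proof. The diagnosis is made "Based on medical history, clinical manifestations, radiological exams, laboratory tests, and possible histological samples".

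Other sections bear on how these criteria work:

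- **Interventions (2.4, Table 3):** moxifloxacin is given in the short-course arm only.
- **Data collection (2.5, Table 4):** smear and culture are scheduled at every visit to month 36 and at a possible poor treatment response. The rapid molecular test is marked at baseline only.
- **Secondary outcomes (2.6.2):** microbiological ineligibility is recognised as a reason for stopping assigned treatment.
- **Sample size (2.7):** "Considering a 10% dropout rate, a sample size of 150 per arm (300 in total) will give 80% power". Section 2.8 describes the 10% as an allowance for loss to follow-up.
- **Statistical analysis (2.9):** "The efficacy analysis will use intention-to-treat, per-protocol, and as-treated populations". The article does not say how criteria 14 and 15 enter these sets.

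**The concern.** An exclusion applied after randomisation is harmless when it depends only on facts fixed before treatment began, even if the laboratory result arrives later. Neither criterion is limited in that way.

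Criterion 15 reaches specimens taken at any later time. A participant who completes treatment, recurs, and yields an isolate with newly acquired resistance meets it. That participant is a treatment failure, yet the text classes them as excluded. Because only one arm contains a fluoroquinolone, acquired fluoroquinolone resistance would tend to arise in the short-course arm, and removing such cases moves the comparison towards non-inferiority.

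Criterion 14 uses a specimen taken after two weeks of different regimens. For some participants, staying in the analysed set then depends on something the assigned treatment can influence.

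The comparison is open-label and few events are expected, so which participants count should be fixed by wording that leaves no choice once results are known.

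**Working it through.** **1. Reproducing the plan's sample size.** Inputs from section 2.7: recurrence 5% in both arms, margin 6.6 points, one-sided alpha 5% (z = 1.645), power 80% (z = 0.8416), dropout 10%.

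n per arm = (1.645 + 0.8416)² × 2 × 0.05 × 0.95 / 0.066² = 134.8, so 135. Then 135 / 0.9 = 150 per arm, 300 in total. This matches the plan exactly. Power with 135 per arm is 80.0%. The 10% allowance is fully used by loss to follow-up, and nothing is left for criteria 14 and 15 in a set that applies them.

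**2. Expected events.** 5% of 135 = 6.75, so about 7 recurrences per arm.

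**3. What one deletion can do.** Upper one-sided 95% bound = difference + 1.645 × SE, with SE = √(p₁(1−p₁)/n₁ + p₀(1−p₀)/n₀).

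| Short-course | Long-course | Difference (points) | SE (points) | Upper bound (points) | Against 6.6 |
|---|---|---|---|---|---|
| 9/135 | 6/135 | 2.22 | 2.78 | 6.8 | fails |
| 8/134 (one resistant recurrence removed) | 6/135 | 1.53 | 2.71 | 6.0 | passes |
| 10/135 | 7/135 | 2.22 | 2.95 | 7.1 | fails |
| 9/134 (one removed) | 7/135 | 1.53 | 2.88 | 6.3 | passes |

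These cases are chosen to lie near the margin. At 7/135 in each arm the bound is 4.4 points, and at 9/135 against 7/135 it is 6.2. Both pass without any deletion.

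**4. Error rate when the true difference equals the margin.** Assume true recurrence of 11.6% against 5%, 135 per arm and the same bound. Non-inferiority is wrongly declared in 5.9% of trials with no deletion. If 10% or 20% of short-course recurrences are deleted, this becomes about 11% or 18%. If the same shares are deleted in both arms, it becomes about 8% or 12%. The deletion shares are assumptions, since the article gives no resistance rate.

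**5. Criterion 14.** Exclusion requires no Mtb in any of the three samples. Anyone positive at screening or baseline stays whatever week 2 shows, so the week-2 result decides only for those negative on both earlier samples. Inclusion criterion 2 makes it likely that such participants exist. The article gives neither their number nor a week-2 yield by arm, so no bias can be calculated.

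**6. Power in a set that applies the exclusions.** Power = Φ(0.066 / √(2 × 0.05 × 0.95 / n) − 1.645), with n = 135 × (1 − share excluded). The share is assumed.

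| Share excluded | n per arm | Power |
|---|---|---|
| 0% | 135 | 80.0% |
| 10% | 121.5 | 76.3% |
| 20% | 108 | 71.9% |
| 30% | 94.5 | 66.9% |

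**The case against.** Criterion 15 sits in an eligibility table, and section 2.6.2 treats microbiological ineligibility as a reason for stopping treatment, which suits an early, entry-type check. The reference to samples after the study may be loose wording for after enrolment. Recurrence is defined by pain and imaging and needs no isolate, and Table 4 lists no later susceptibility test. All this makes it plausible that nobody intends to delete late recurrences. It does not cure the text: even read as after enrolment, the criterion admits isolates obtained on treatment or at recurrence, and cultures are scheduled at exactly those times.

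Section 2.9 names an intention-to-treat population. If that set keeps everyone randomised and leads the analysis, neither the deletions nor the power loss touches it. This stands. A reader might infer that the stated 80% power or the 150 per arm is wrong; the documents do not support that, because the figure reproduces exactly and any loss depends on the analysis set and on an exclusion rate they do not give.

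A reader might also infer that the week-2 rule pushes the result towards non-inferiority. That does not follow either. The rule affects only participants negative on both earlier samples, and nothing in the article shows the direction.

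Finally, the one-event reversal is a borderline case. With 7 long-course events, removing one short-course recurrence changes the conclusion only when there are exactly 10. Resistance to rifampin or isoniazid can also arise in the long-course arm, so deletions need not be one-sided.

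**Conclusion.** The point holds for the wording of the two criteria. Criterion 15, followed as written, can remove recurrences with acquired resistance from any analysis set that applies it. The presence of a fluoroquinolone in one arm only makes removal in favour of non-inferiority the likelier direction. With about 7 events expected per arm, one removal can move a borderline upper bound by about 0.8 points (6.8 to 6.0) across the 6.6-point margin. How often this would happen cannot be derived from the article.

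Criterion 14 makes retention depend on an on-treatment sample in a limited subgroup, with unknown size and direction.

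The 80% power is correct for an analysis of all randomised participants with 10% lost to follow-up. It should not be carried over to a confirmed, drug-susceptible set, where it would be about 76%, 72% or 67% if 10%, 20% or 30% were excluded. The article does not show that failures will in fact be deleted, or that its intention-to-treat set is anything other than all randomised participants. It leaves the exclusions and the analysis sets unreconciled.

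**What to change.** 1. Base criteria 14 and 15 only on specimens collected before the first study dose, whatever the date of the result. Delete the reference to week 2 from criterion 14 and the reference to samples after the study from criterion 15.
2. State that resistance first found in a later specimen is not a ground for exclusion from analysis, and that a recurrence with such resistance counts as a recurrence. This concerns analysis only; clinical management of these participants is a separate matter.
3. State that the intention-to-treat set contains all randomised participants, and report the confirmed, drug-susceptible set alongside it. Both are needed: participants without confirmed disease can pull the arms together and so favour non-inferiority, while exclusions can disturb the randomised comparison.
4. Keep the 80% power statement for the intention-to-treat set. For the confirmed set, give power as conditional on a stated exclusion rate. If 80% is wanted there too, 135 / (0.9 × (1 − share)) gives 167 per arm at 10% excluded and 188 at 20%.

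The cost is small: wording in Table 2 and the analysis plan, with the rapid molecular test already scheduled at baseline. Dropping the week-2 sample makes the confirmed set slightly smaller, and its stated power will look less favourable. Recruitment grows only if the sponsor chooses to power that set at 80%.

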### Randomization

2.3

A blocked randomization approach with stratification will be employed to allocate eligible patients into the short-course regimen [6-month anti-TB regimen] group and the empirical long-course regimen [12-month anti-TB regimen] group in a 1:1 ratio. The participants will be stratified according to the study sites. All research staff will undergo uniform training to ensure consistency across all study sites. The randomization list will be generated using SAS v9.4, and the allocation sequence will be carried out by the trial statistician via the central phone system. Both participants and investigators will be aware of the allocation, as the study will not be blinded.

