#### Primary outcomes

2.6.1

The primary outcomes are TB-recurrence rate of spinal tuberculosis at 24 months after completion of treatment (efficacy outcome, non-inferiority aspect) and the proportion of participants with grade 3 or higher adverse events (AEs) during study medication (safety outcome, superiority aspect). The recurrence of spinal tuberculosis is defined by the reappearance of pain, with or without sinus formation, loosening or displacement of internal fixation on X-ray, and confirmed by postoperative computed tomography or magnetic resonance imaging showing increased local abscess, bone graft absorption, new sequestrum formation, or aggravated bone destruction (Ren et al., 2016). AEs are graded per CTCAE v5.0, with grade 3+ events defined as severe functional impairment, life-threatening complications, or death; causality is adjudicated by the Safety Monitoring Committee using WHO-UMC criteria.

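### Recurrence is a pain-led, image-judged primary outcome in a fully open-label trial with no masked assessment stated; with about 7 events expected per arm, a few arm-dependent calls could move the non-inferiority result either way

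*Protocol article*

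**What the plan says.** Section 2.3 (Randomization) describes an open-label trial: "Both participants and investigators will be aware of the allocation, as the study will not be blinded". Nothing there or elsewhere in the article exempts outcome assessment.

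Section 2.6.1 (Primary outcomes) sets out the efficacy outcome: "The recurrence of spinal tuberculosis is defined by the reappearance of pain, with or without sinus formation". Fixation changes on X-ray are also listed, and the event must be "confirmed by postoperative computed tomography or magnetic resonance imaging showing increased local abscess" or one of several other structural changes, among them worsening bone destruction. Some of these findings, such as a larger abscess or worse destruction, are judged by comparison with an earlier state.

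The same section names one adjudication, and it concerns adverse events: "causality is adjudicated by the Safety Monitoring Committee using WHO-UMC criteria". No adjudicator, central reading or masked reader is named for recurrence.

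Table 4 in section 2.5 records symptoms at all 13 scheduled post-baseline visits. It lists no spinal X-ray, CT or MRI at any visit; its only imaging row is a chest radiograph.

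**The concern.** The first step towards an event is a complaint from a patient who knows the arm. Because Table 4 schedules no spinal imaging, the scan appears to follow from symptoms or from a clinician's request, and that clinician also knows the arm. The last step is a reading of change on CT or MRI, with no statement that the reader is kept unaware of the arm.

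The arms differ visibly in duration (26 v 52 weeks, section 2.4), so expectations about relapse after the shorter course could plausibly affect these steps. Confidence in the short course could lead to borderline scans being read as stable, which favours a false claim of non-inferiority. Suspicion of it could lead to borderline scans being read as recurrence, which costs power. Treatment cannot reasonably be masked here, but the reading of a scan can.

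**Working it through.** **Inputs** (section 2.7 unless noted): recurrence 5% in both arms; margin 6.6 points; one-sided type I error 5%; power 80%; dropout 10%; 150 per arm; 1:1 allocation (section 2.3).

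**The plan's own figure.** With the unpooled normal approximation,

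n = (1.645 + 0.842)² × (2 × 0.05 × 0.95) / 0.066² = 134.8, so 135 evaluable per arm, and 135 / 0.90 = 150. The stated sample size reproduces.

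**Expected events.** 135 × 0.05 = 6.75 per arm. If the short-course rate lies at the margin, 5% + 6.6% = 11.6%, its expected count is 135 × 0.116 = 15.7. One percentage point is 1.35 patients; two points are 2.7.

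**Formula for the effect of misclassification.** With recorded rates pT (short course) and pC (long course),

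P(declare non-inferiority) = Φ[(0.066 − (pT − pC)) / SE − 1.645], where SE = √[(pC(1 − pC) + pT(1 − pT)) / 135].

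The article gives no misclassification rate, so the shifts below are assumptions, shown as a range.

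*Under-calling on the short course, true rates 11.6% v 5% (every non-inferiority claim is false):*
- no shift: SE 0.0333, (0.066 − 0.066)/0.0333 − 1.645 = −1.645, giving 5.0%
- 1 point (10.6% recorded): SE 0.0325, 0.010/0.0325 − 1.645 = −1.337, giving 9.1%
- 2 points (9.6% recorded): SE 0.0315, 0.020/0.0315 − 1.645 = −1.011, giving 15.6%

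*Over-calling on the short course, true rates 5% v 5%:*
- no shift: SE 0.0265, 0.066/0.0265 − 1.645 = 0.843, giving 80.0% power
- 1 point (6% recorded): SE 0.0277, 0.056/0.0277 − 1.645 = 0.374, giving 64.6%
- 2 points (7% recorded): SE 0.0289, 0.046/0.0289 − 1.645 = −0.052, giving 47.9%

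*Over-calling on the long course, short course truly at 11.6%:* recording 6% or 7% instead of 5% gives a false claim in 8.8% or 14.1%.

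**Cross-check.** Exact binomial enumeration of the same unpooled test gives 5.9%, 10.4% and 17.4% for the under-calling cases, and 80.5%, 65.8% and 49.8% for the over-calling cases. The approximation is not driving the result.

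**In single patients.** Take 7 recurrences among 135 on the long course. With 9 on the short course, the one-sided 95% upper bound for the difference is 1.48 + 4.72 = 6.2 points, and non-inferiority is met. With 10 it is 2.22 + 4.86 = 7.1 points, and it is not met. At that boundary one call decides the trial.

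**The case against.** The strongest objection is that this is silence in a condensed article, not an error. The sentence on blinding is accurate, and open-label treatment is reasonable when the arms differ in both drugs and duration. Who reads scans may be settled in the full protocol or supplement, which are not at hand. This stands in part. A reader might infer that investigators who know the arm judge recurrence. The article does not say so: it names no judge and no reader, and section 2.3 speaks only of participants and investigators. What remains is that an unqualified statement of no blinding sits beside a comparative, image-based primary outcome, while the article does name an adjudicator for adverse event causality.

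Second, pain alone is not an event. Confirmation on CT or MRI is mandatory, which limits subjective calls. That is correct, and it is why masking the reading is worthwhile. It does not remove judgement from borderline changes.

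Third, the size depends on assumed shifts. This also stands. In the 11.6% scenario, 2 points means missing 2.7 of 15.7 short-course events, about one in six, which is a substantial error rate. The 1-point rows show the milder case.

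Fourth, it is tempting to hand recurrence to the Safety Monitoring Committee with all dates removed. The documents do not support that. The committee is described only in a safety role, is not shown to read spinal imaging, and may learn the arm through causality review. Removing all dates would also defeat a judgement of enlargement or worsening.

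Finally, masked reading acts only on scans that have been requested. It cannot recover pain that was not reported or a scan that was not ordered. This stands in full.

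**Conclusion.** The concern holds in a limited form. The article fixes an open-label design without exception, defines the primary efficacy outcome by pain plus a comparative reading of images, and states no masked assessment. It does not establish that unmasked people will make the judgement, and it does not make the open-label design wrong.

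The bias could go in either direction. Under assumed shifts of 1 or 2 points with 135 evaluable per arm, false non-inferiority rises from 5% to about 9% or 16%, or power falls from 80% to about 65% or 48%. These figures show how sensitive the result is; they do not predict that such shifts will occur. Masked reading would remove only the share that arises when scans are interpreted. The point is worth acting on because few events decide the trial and the remedy is inexpensive.

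**What to change.** State in section 2.6.1 that:
- the CT or MRI already required to confirm recurrence is reported by the usual radiologist, in comparison with the patient's earlier scans, with scan dates kept;
- arm, regimen and treatment dates are left off the request;
- this masked report decides the imaging criterion of the primary outcome for every suspected case in both arms.

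Acknowledge as a remaining limitation that pain reporting and the decision to order a scan stay open to knowledge of the arm.

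The sample size stays at 150 per arm, and no extra readers or scans are needed. Coordinators must prepare requests without arm information for all suspected cases. The assumed rates imply about 14 true recurrences (2 × 6.75 = 13.5); suspected cases could be considerably more, and the article gives no figure. Masking may be imperfect where the radiologist can open the clinical record.
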